We will assess the effectiveness of the S4R Toolbox through a cRCT (test case 1), a pre-post evaluation (test cases 2-4), and a cost-effectiveness evaluation (test case 1). In both study designs, the primary outcome will be health care workers’ mental well-being, measured using the SWEMWBS. Secondary outcome measures include individual resilience, organizational resilience capacities, burnout, turnover intention, self-assessed health, and, for informal caregivers, family involvement in care and caregiver self-assessment. In addition, sick leave will be assessed using public sick leave records where available. The effectiveness, cost-effectiveness, and cRCT analyses of the S4R intervention will provide information for decision makers in organizations at both the national and European Union (EU) levels.

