A 30% response rate was used as a conservative planning assumption for this pragmatic workforce trial in older adult care to reduce the risk of overestimating the effective sample size under real-world conditions. Participation and retention will be supported through leadership engagement, brief, mobile-friendly questionnaires, repeated reminders, and monitoring of response rates at each measurement time point.

The primary outcome measure, the SWEMWBS, will be treated as a continuous outcome. The primary analysis will follow the intention-to-treat principle at the home care service (cluster) level. Noncompliance with the intervention may attenuate the observed intervention effect. Linear mixed-effects models will be used, including random intercepts for clusters. Group (intervention vs control) will be included as a fixed effect, and SWEMWBS (mental well-being) will be the primary outcome. Other outcomes (burnout, turnover intention, caregiver burden, etc) will be analyzed as secondary end points.

Analyses will follow the intention-to-treat principle. A complier average causal effect analysis will also be conducted to account for variation in exposure to the intervention.

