#### Cost-Effectiveness Analysis

Cost-effectiveness analysis will be conducted only for the cRCT study design (Norway and Finland).

The primary outcome will be SWEMWBS, with effectiveness assessed using the same methods described in the previous section.

The costs of the intervention will be based on the time spent by leaders, health care workers, and researchers implementing the S4R Toolbox. The learning collaboratives support the leaders and are therefore expected to influence the effectiveness of the Toolbox. The cost data will be based on the following:

Minutes that health care workers use the Toolbox (data source: log files from the digital Toolbox).Hours that leaders and health care workers spend in meetings discussing the themes of the Toolbox and planning deimplementation or other workplace changes (data sources: learning collaborative meetings and interviews with leaders).Hours that leaders and researchers spend participating in local learning collaboratives (data source: notes/minutes from the learning collaboratives, including time and participants).The time spent by health care workers, leaders, and researchers will be valued using nationally representative wages and social security contributions.

The time horizon for the analysis is 1 year; therefore, no discounting will be applied. The analysis adopts the perspectives of 2 funders: the participating organizations, which cover the costs of leaders’ and health care workers’ time, and the S4R project funding organization (EU), which covers the costs of researchers’ support for implementing the Toolbox.

We use intention-to-treat based analyses and evaluated the incremental net monetary benefit of the Toolbox compared to no Toolbox ("practice as usual"). We evaluated incremental net monetary benefit (NMB) in comparing the alternatives. NMB is calculated by multiplying the observed effects by the decision-makers’ willingness to pay, λ, for an extra unit of effectiveness, and then subtracting the observed cost [37,38]. As the willingness to pay for one extra unit of effectiveness in SWEMWBS is unstated, we use a range of values.

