As a sensitivity analysis, we will use an algorithm to convert changes in SWEMWBS scores into WELLBY (Wellbeing-Adjusted Life Year) units [39-41]. WELLBYs have been monetized and can therefore provide a monetary estimate of effectiveness. This analysis will also provide an opportunity to interpret the results of the cost-effectiveness analysis across the range of willingness-to-pay values.

To further support the robustness of our analysis, we will also conduct a cost-benefit analysis. For this analysis, we will collect data from the participating organizations (work units) on sickness absence (spells and days), staff resignations, turnover, disability pensions, and personnel survey results for the years 2023-2026. Where possible, these measures will be monetized using national recommendations, statistics, reports, and research.

The S4R project does not aim to estimate a single pooled effect across countries. The participating health care systems differ substantially in structure, governance, workforce composition, and the availability of formal older adult care services. Because of this heterogeneity, the project follows the MRC guidance for evaluating complex interventions, which explicitly recommends that evaluation designs be adapted to local feasibility and contextual conditions.

In Norway and Finland, organizational structures allow randomization of home care units, making a cRCT feasible and appropriate for evaluating both effectiveness and cost-effectiveness. In the other participating countries, randomization was not feasible because of organizational differences and the absence of comparable units. For these countries, a pre-post evaluation is methodologically appropriate and enables examination of within-country change. This hybrid approach preserves scientific rigor by using the strongest possible design where feasible while ensuring validity and contextual relevance across diverse older adult care systems.

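### For the cRCT, sick leave should be prespecified from the work-unit absence records already planned for the economic analysis, and their window extended past 2026 to cover the full program year

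*Protocol article*

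**What the plan says.** Sick leave appears in three places in the protocol article.

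- **Implementation, Evaluation, and Finalization Phase, Overview (Methods).** The primary outcome in both designs is SWEMWBS. The secondary list follows: "Secondary outcome measures include individual resilience, organizational resilience capacities, burnout, turnover intention, self-assessed health, and, for informal caregivers", with two caregiver measures after it. Sick leave is not in that list. The next sentence adds it: "In addition, sick leave will be assessed using public sick leave records where available". The paragraph covers both the cRCT and the pre-post evaluations in test cases 2-4.
- **Cost-Effectiveness Analysis.** This section is restricted to the cRCT countries. A supporting analysis is announced: "To further support the robustness of our analysis, we will also conduct a cost-benefit analysis". For it, "we will collect data from the participating organizations (work units) on sickness absence (spells and days), staff resignations, turnover, disability pensions", and the list closes with "personnel survey results for the years 2023-2026". No availability condition is attached to the collection; the only such qualifier concerns turning the measures into money.
- **Resilience and Mental Well-Being Factors (input phase).** Sick leave is among the constructs measured at baseline at the recruited sites in each country, but none of the instruments named there is specific to it.

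The cRCT section does not name sick leave: "Other outcomes (burnout, turnover intention, caregiver burden, etc) will be analyzed as secondary end points". On survey participation it says: "A 30% response rate was used as a conservative planning assumption".

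**The concern.** The effectiveness evaluation takes sick leave from a source that may exist for some units and not others. The economic section of the same article plans to obtain absence data from the work units themselves, with no such condition, but gives them no role in the randomized comparison of effectiveness.

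This matters because of what the other outcomes are. SWEMWBS and the listed secondary scales are self-reported. Control units do not implement the Toolbox, so workers can plausibly tell their arm; this is an inference, since the article does not describe blinding. About 30% are expected to answer, and the missing-data section itself provides for attrition that differs between arms. Absence totals held by the unit do not pass through the survey. They would give a separate view of the intervention in the same units, with each unit's own history as baseline. Survey responses are also to be collected anonymously, which makes linking individuals to outside records difficult; aggregate unit data avoid that.

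**Working it through.** The article gives no sample size, power or expected rate for sick leave, so there is no stated figure to reproduce. The check compares the two sources and then does simple arithmetic.

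**1. The two sources side by side**

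| | Effectiveness evaluation | Economic section |
|---|---|---|
| Source | Public records | Participating work units |
| Condition | Only where available | None stated for collection |
| Measure | Not specified | Spells and days |
| Period | Not specified | 2023-2026 |
| Countries | All test cases | Norway and Finland |
| Stated use | Effectiveness | Cost-benefit analysis |

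No sentence links the two columns.

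**2. Who is covered** (cRCT section: 30 clusters, about 30 workers each, about 9 respondents each)

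- Eligible workers: 30 × 30 = 900.
- Expected survey respondents: 30 × 9 = 270, and 270 / 900 = 30%.

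This is a difference in coverage, not in precision. Unit-level absence gives one value per unit, so the comparison has 30 data points, or 15 per arm under equal allocation.

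**3. Does the record window fit the program?** The start is April 2026 (Results, implementation phase) and the duration is 12 months (S4R Intervention Design Development Phase). The years are read as applying to the whole list of records.

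- Program period: April 2026 to about March 2027.
- Inside the window: April-December 2026 = 9 months. 9 / 12 = 75%.
- Outside the window: January-March 2027 = 3 months.
- Pre-intervention: 2023, 2024 and 2025 = 36 months, plus January-March 2026 = 3 months, giving 39 months.

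If units supply annual totals, the 2026 figure mixes 3 pre-intervention months with 9 program months, and the two cannot be separated. Dated or monthly data are needed.

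**4. What baseline adjustment could give.** With correlation r between a unit's pre-intervention rate and its program-year rate, adjustment removes a share r² of the between-unit variance and multiplies the standard error by √(1 − r²).

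- r = 0.5: 0.5² = 25% removed; √0.75 = 0.87.
- r = 0.7: 0.7² = 49% removed; √0.51 = 0.71.

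The values of r are an assumption; the article gives none. They describe a single correlation and do not model the average of three earlier years.

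**The case against.** Four stronger readings are tempting, and the article supports none of them.

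- **That the article contradicts itself.** It does not. Separate analyses may use separate sources, and the scopes differ: the effectiveness sentence covers all test cases, including private residential care and a Romanian hospital, where an availability condition is ordinary. The work-unit records belong to the cRCT countries.
- **That sick leave is a secondary outcome measured only from public records.** Its secondary status is never stated, and it is also listed among the baseline measures.
- **That the trial will report two diverging sick-leave results.** Test case 1 is public home care, so the public records might be the same employer data. The article does not say.
- **That work-unit records have no non-response and triple the sample.** No sentence promises complete records from every unit, and 900 against 270 is not a gain in precision.

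It can also be argued that the absence data are not wasted, since a cost-benefit analysis in a randomized setting would ordinarily compare them between arms; that source, unit and period for a minor outcome are normally left to the full protocol or analysis plan; and that absence is a different construct from well-being. The first is likely, but such a comparison is not stated as an effectiveness result. The second would decide the matter if the article were silent, but it names a source in two places, and the point concerns what it names. The third stands: absence complements SWEMWBS and cannot validate it.

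**Conclusion.** The point holds as a minor, cheap improvement to the cRCT. The article attaches the conditional source to effectiveness and the unconditional one to the cost-benefit analysis only, and leaves open whether they are the same. An arm comparison on work-unit records would not depend on the 30% survey response and could use about three pre-intervention years per unit.

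The records as planned are not sufficient for that comparison, because they cover about 9 of the 12 program months. The article itself says that organizational change needs time, so the missing last quarter may be an informative one. The same shortfall bears on the cost-benefit analysis, which sits in a section with a one-year horizon.

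This rests on the scheduled April 2026 start, a full 12-month program and the 2023-2026 limit applying to absence data. Any precision gain depends on the assumed correlation. SWEMWBS, its analysis and its power calculation are unaffected.

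**What to change.** For the cRCT in Norway and Finland:

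1. Prespecify sick leave as unit-level absence, in days per employed person-year with spells as supportive, from the work-unit records of all 30 randomized units. State whether it is a secondary outcome.
2. Compare arms over the 12-month program with a cluster-level model adjusted for the same unit's pre-intervention rate.
3. Extend the record window from the end of 2026 to the end of the program, about March 2027. Request dated or monthly data, with the headcount or person-time needed for the denominator, so that January-March 2026 counts as pre-intervention.
4. Use public records as a cross-check, and say whether they are the same data.

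For test cases 2-4, public records where they exist can remain the source.

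The cost is an outcome definition, one extra model and about three more months of records. The limits are that the outcome is aggregate, has 30 data points, includes staff who did not answer the survey, and is only as complete as the units' deliveries. Sites are already randomized, so the change should be recorded before outcome data are seen.

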#### Pre-Post Evaluation (Test Cases 2-4)

Changes from baseline to postintervention will be examined using mixed-effects regression models. Individuals will be nested within organizational units, with random intercepts included for organizational units. Time will be entered as a fixed effect. Standardized effect sizes (Cohen *d*) will be calculated to aid interpretation.

For countries using a pre-post evaluation, a sample of 250-500 participants per country is sufficient to

Detect moderate changes (effect size, *d*≈0.25-0.36) with 95% power (taking clustering into account, assuming an intraclass correlation coefficient [ICC] of 0.05).Estimate within-country effects using mixed-effects models.Explore relevant subgroup differences.

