## Methods

### Study Design and Phases

The S4R project applies an exploratory, longitudinal, mixed-methods co-design methodology to achieve the intended project results, outcomes, and impacts [12] (see Figure 2). It comprises 4 phases and 5 main work packages (WPs):

Input phase (WP1 and WP2)Co-design of the S4R Toolbox and prototype testing phase (WP3)Implementation, evaluation, and finalization phase (WP4)Output phase (WP5)

The choice of methodology is based on and aligned with the project objectives of developing, implementing, and evaluating a research-based toolbox to support leaders. The process will be based on the Medical Research Council’s (MRC) guidelines [13] for developing, implementing, and evaluating complex interventions to improve health care. This framework emphasizes the importance of context, including adaptation to local settings, to ensure success in practice.

The countries included in the project were selected because they organize health care services differently, allowing the S4R Toolbox to be tested under varying conditions. As such, the objective is not to compare outcomes across countries but rather to ensure a positive impact (measurable, observable, or experienced improvements in the resilience and mental well-being of health care workers in older adult care, supported by strengthened leadership practices and improved working conditions) in each setting. The test sites in each country will be recruited to contribute to data collection (interviews and surveys) during the input phase (pretest), toolbox testing, and data collection (interviews, observations, and surveys to enable process evaluation and assess the effectiveness and cost-effectiveness of the toolbox) during the implementation and evaluation phase (posttest). The test sites will include units with a total sample size of 250-500 participants in each country, consisting of health care workers, health care leaders, and informal caregivers. This will provide the basis for pre- to posttest comparisons for test cases 2-4 (see Figure 3). In addition, test case 1 (Norway and Finland) will participate in a cluster randomized controlled trial (cRCT) to assess the effectiveness and cost-effectiveness of the intervention (see Figure 3 for the different test cases).

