#### cRCT (Norway and Finland; Test Case 1)

The S4R Toolbox will be evaluated in a 2-arm cRCT in 2 countries (Finland and Norway). An equal allocation ratio will be used for the 2 groups: an intervention arm, in which the S4R Toolbox is implemented by health care leaders, and a control arm, in which the S4R Toolbox is not implemented by health care leaders. The cRCT will include 30 clusters with approximately 30 health care workers per cluster. Accounting for clustering (ICC=0.05), an expected 30% response rate (approximately 9 respondents per cluster), and 6 repeated measurements (baseline plus 5 follow-up assessments) with a plausible within-person correlation of 0.5-0.7, the cRCT has 95% power to detect standardized effect sizes of approximately *d*=0.28-0.32 for mental well-being. The 6 measurement time points were chosen to align with the planned phases of Toolbox use and feasible data collection windows in the participating services. This pragmatic schedule enables monitoring of early adoption and engagement, as well as whether changes are sustained over the intervention period.

The sample size calculations assumed an ICC of 0.05 and an average of approximately 9 respondents per cluster (30% response from approximately 30 eligible workers). The assumed ICC of 0.05 was selected based on previous cluster randomized trials in primary care, home care, and organizational intervention studies, in which ICCs for psychosocial and workforce-related outcomes commonly ranged from 0.01 to 0.10. Given the lack of precise prior ICC estimates for mental well-being outcomes in older adult home care services, an ICC of 0.05 was considered a conservative and appropriate planning value. This corresponds to a cluster design effect of 1.40. To assess the robustness of the findings to uncertainty in the ICC, we conducted sensitivity analyses using ICC values of 0.03, 0.08, and 0.10 (design effects of 1.24, 1.64, and 1.80, respectively). Holding all other assumptions constant, the detectable standardized effect size ranged from *d*=0.26-0.30 (ICC=0.03) to *d*=0.30-0.35 (ICC=0.08) and *d*=0.32-0.36 (ICC=0.10), compared with *d*=0.28-0.32 under the base-case ICC of 0.05. These findings indicate that the trial is sufficiently powered to detect small-to-moderate improvements in the primary outcome.

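### The pre-post model names a random intercept for units but no within-person term, so if workers' two responses are linked the standard error of the time effect will be wrong

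*Protocol article*

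**What the plan says.** The section Pre-Post Evaluation (Test Cases 2-4) specifies the analysis in three steps. The target is a change between two time points: "Changes from baseline to postintervention will be examined using mixed-effects regression models". The random part is "Individuals will be nested within organizational units, with random intercepts included for organizational units". The fixed part is "Time will be entered as a fixed effect". No random effect for the individual and no within-person covariance is named.

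The same section holds that "a sample of 250-500 participants per country is sufficient to" detect a standardized change of about 0.25-0.36 with 95% power at an ICC of 0.05. It gives no within-person correlation and no unit size. Both appear only in the cRCT section: "6 repeated measurements (baseline plus 5 follow-up assessments) with a plausible within-person correlation of 0.5-0.7" and "The cRCT will include 30 clusters with approximately 30 health care workers per cluster".

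On whether the same workers are followed, the article points both ways:

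- Study Design and Phases calls the project longitudinal.
- Handling of Missing Data foresees people dropping out after baseline. That section is written partly for the cRCT, so for test cases 2-4 it is an indirect sign.
- Research Ethics says that data are pseudonymized at source, which would allow linkage. It also says that survey responses are gathered anonymously, which would not.

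**The concern.** When the same worker answers before and after, the time effect is a within-person contrast, and stable differences between workers cancel out of it. A model with a unit intercept alone treats the two scores as coming from two different people in the same unit. The stable between-worker variance then stays in the residual, and the reported standard error is larger than the real one. The estimate of change is not biased; its confidence interval and p value are wrong.

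A second omission works in the other direction. The section on implementation lets leaders adapt the format, frequency and integration of the Toolbox, so units may change by different amounts. A single unit intercept has no place for that variation, and leaving it out makes the standard error too small. What is at stake is whether the intervals in the pre-post countries can be trusted, in either direction.

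**Working it through.** **Inputs.** ICC 0.05 and n = 250-500 per country come from the pre-post section. The within-person correlation r = 0.5-0.7 and about 30 workers per unit are borrowed from the cRCT section. Two-sided alpha of 0.05 is assumed, so the multiplier for 95% power is 1.960 + 1.645 = 3.605. Outcome variance is set to 1.

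**1. The plan's own figure.** With m = 30 the design effect is 1 + 29 × 0.05 = 2.45. Taking the variance of change as 1 (r = 0.5, or d on the change scale):

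- n = 250: 3.605 × √(2.45/250) = 0.357
- n = 500: 3.605 × √(2.45/500) = 0.252

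This reproduces 0.36 and 0.25. An unpaired formula, 3.605 × √(2 × DE/n), also fits with small units: m = 5 (DE 1.20) gives 0.353 and 0.250, and m = 6 (DE 1.25) gives 0.360 and 0.255. The stated figure therefore does not show whether pairing was assumed.

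**2. Full linkage, units changing alike.** The unit-only model reports Var(time) = 2(1 − ICC)/n = 1.90/n. The true variance is 2(1 − r)/n, which is 1.00/n at r = 0.5 and 0.60/n at r = 0.7. The ratio of standard errors is √((1 − ICC)/(1 − r)):

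- r = 0.5: √(0.95/0.50) = 1.38
- r = 0.7: √(0.95/0.30) = 1.78

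Simulation with 60 replicates per setting agrees: 1.38 and 1.78 for 10 units of 30, and 1.36 and 1.75 for 30 units of 9.

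**3. Partial linkage.** If a share f of workers is linked, the reported SE over the true SE of the same estimate is √(0.95/(0.95 − f(r − 0.05))).

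| Share linked | r = 0.5 | r = 0.7 |
|---|---|---|
| 100% | 1.38 | 1.78 |
| 70% | 1.22 | 1.39 |
| 50% | 1.14 | 1.23 |
| 30% | 1.08 | 1.12 |
| 0% | 1.00 | 1.00 |

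**4. Units changing by different amounts.** Let c be the correlation of a unit's own effect between the two waves, with full linkage and m workers per unit. The reported variance per unit is 2(1 − 0.05c)/m. The true variance is 2[(0.95 − r + 0.05c)/m + 0.05(1 − c)]. For m = 30:

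| c | r = 0.5 | r = 0.7 |
|---|---|---|
| 1.0 | 1.38 | 1.78 |
| 0.9 | 1.22 | 1.46 |
| 0.8 | 1.10 | 1.28 |
| 0.5 | 0.89 | 0.98 |

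At c = 0.5 the reported standard error is too small. For m = 9 the ratios at c = 0.5 are still 1.18 and 1.40, so the direction depends on unit size.

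**5. Detectable change at 95% power, full linkage, c = 1.** This is 3.605 × √(V/n), with V = 1.90 for the unit-only model.

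| Model | n = 250 | n = 500 |
|---|---|---|
| Unit intercept only | 0.31 | 0.22 |
| Plus worker intercept, r = 0.5 | 0.23 | 0.16 |
| Plus worker intercept, r = 0.7 | 0.18 | 0.12 |

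The unit-only values are still below the stated 0.36 and 0.25.

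**The case against.** The article is a condensed account, and its sentence does not rule out a worker term; the full covariance structure may stand in an analysis plan that is not shown. That has some weight. But the article goes beyond a general statement: it gives the hierarchy, the random part and the fixed part, and the worker is missing from the random part. Followed as written on linked data, it gives a wrong standard error.

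The stronger objection is that responses may not be linked at all. If anonymous collection is meant literally, the ratio is 1.00 and a worker intercept cannot be fitted. Even with linkage, full overlap is optimistic. If the input-phase survey (months 1-17) is the baseline, and a 12-month program starts no earlier than month 22, the gap to the post survey is at least 22 + 12 − 17 = 17 months, in a workforce with known retention problems. This part stands, and it limits the size of the point.

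Three stronger readings are tempting, and the documents do not support them:

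- **That the standard error is 1.4-1.8 times too large throughout.** This needs full linkage, a correlation borrowed from another design, and units that all change alike. It also need not apply to every pre-post country, since Australia evaluates independently.
- **That the stated detectable change presupposes pairing.** An unpaired calculation with 5-6 respondents per unit fits equally well.
- **That changes of the planned size would be missed.** With 250-500 analysed they would not. The total is a "total sample size of 250-500 participants in each country, consisting of health care workers, health care leaders, and informal caregivers", while the primary outcome concerns workers only, so fewer may enter that analysis. The documents give no split for test cases 2-4, so a shortfall cannot be established from them.

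**Conclusion.** The point holds in conditional form. The written model omits the within-person term. If responses are linked, which the documents suggest but do not settle, the standard error of the time effect is wrong.

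The upper end, 1.38-1.78, rests on full linkage, r of 0.5-0.7 and no unit-by-time variation. With 30-50% linked it is 1.08-1.23. With strong unit-by-time variation and units of about 30 it can fall below 1.

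Where units change alike, the consequence is needlessly wide intervals, with no added false-positive risk. The stated detectable change of 0.25-0.36 is not overturned by this point alone. The correction is worth making because it is almost free and because the text does not say which design is being analysed.

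**What to change.** First, state for test cases 2-4 whether a worker's baseline and post responses can be linked, and reconcile the anonymous collection described in Research Ethics with the dropout patterns in Handling of Missing Data.

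- **If linked:** specify random intercepts for organizational unit and for individual within unit, with time as a fixed effect, and keep workers seen at one wave only. Add a unit-by-time random effect, or small-sample cluster-robust standard errors, where the number of units allows. That number is not stated, and Italy uses one large facility and Romania one public hospital, so this term may not be estimable everywhere.
- **If not linked:** describe the design as repeated cross-sections. A worker intercept then has no role.

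The cost is one or two sentences in the plan and, in the linked case, a pseudonymous identifier kept across waves. The downside is that the unit-by-time term may widen intervals somewhat where units really differ.

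### The pre-post model for test cases 2-4 has a unit intercept only, so where a worker's two surveys are linked it ignores their correlation and the standard error of the change is miscalibrated

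*Protocol article*

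**What the plan says.** The section Pre-Post Evaluation (Test Cases 2-4) fixes the structure of the model in two sentences: "Individuals will be nested within organizational units, with random intercepts included for organizational units" and "Time will be entered as a fixed effect". Individuals are named as a level, but only the unit receives a random effect.

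The same section claims that "a sample of 250-500 participants per country is sufficient to" reach this target: "Detect moderate changes (effect size, *d*≈0.25-0.36", "with 95% power (taking clustering into account, assuming an intraclass correlation coefficient [ICC] of 0.05". It gives no within-person correlation and no cluster size. Study Design and Phases describes that sample as "a total sample size of 250-500 participants in each country, consisting of health care workers, health care leaders, and informal caregivers", so it is not made up of workers alone, although the primary outcome is workers' mental well-being.

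A within-person correlation appears only in the cRCT section: "with a plausible within-person correlation of 0.5-0.7".

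On whether the same person's surveys can be joined, the article points both ways. The design is called longitudinal, and the missing-data section foresees people dropping out after baseline, which suggests a followed cohort. Research Ethics says that data are pseudonymized when collected, but also that survey answers are anonymous.

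**The concern.** A unit intercept makes all answers from one unit equally correlated, whether they come from two colleagues or from one worker at two times. A within-unit change is then judged against the full spread between workers (about 0.95 of the total variance at ICC 0.05). For linked answers the right yardstick is the variance within a worker, which is 1 minus the within-person correlation.

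Test cases 2-4 have no control arm, so the within-country change is their only quantitative estimate of effectiveness. With linked answers and a common change across units, its confidence interval is wider than the data warrant and the precision gained by pairing is lost. With unequal change across units the same model omits another component of variance, and the error can run in the opposite direction.

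**Working it through.** **Inputs.** ICC 0.05 and n = 250-500 come from the pre-post section. The within-person correlation r = 0.5-0.7 comes from the cRCT section and is assumed to carry over. A two-sided 5% test is assumed, since none is stated. Total variance is set to 1. The 250 below are taken as linked workers, also an assumption.

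**1. The plan's own figure.** With d = (1.960 + 1.645) × √(f × DE / n) and DE = 1 + (m − 1) × 0.05:
- A paired test at r = 0.5 (f = 1) with m = 30 has DE = 2.45 and gives d = 0.357 at n = 250 and 0.252 at n = 500.
- Two independent waves of n each (f = 2) with m = 5-6 have DE = 1.20-1.25 and give d = 0.353-0.360 and 0.250-0.255.

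Both reproduce 0.25-0.36. The figure therefore does not show whether a linked cohort or two separate samples was planned.

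**2. SE of the change, full linkage and equal change in every unit (n = 250).**
- Unit intercept only: √(2 × 0.95 / 250) = 0.0872.
- With a worker term, √(2 × (1 − r) / 250): 0.0632 at r = 0.5 and 0.0490 at r = 0.7.
- Ratio √(0.95 / (1 − r)): 1.38 at r = 0.5 and 1.78 at r = 0.7, whatever the sample size.

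**3. Consequences at n = 250.** The printed model rejects when the estimated change exceeds 1.96 × 0.0872 = 0.171 in absolute value.
- Type I error: 2 × [1 − Φ(0.171 / 0.0632)] = 0.7% at r = 0.5, and 0.05% at r = 0.7.
- Power at d = 0.20, printed model: Φ((0.20 − 0.171) / 0.0632) = 68% at r = 0.5, and 72% at r = 0.7.
- Power at d = 0.20, worker term: Φ(0.20 / 0.0632 − 1.96) = 89% at r = 0.5, and 98% at r = 0.7.

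Unit-only models fitted to simulated data (300 runs per setting; 28 units of 9 and 12 units of 30) gave ratios of mean model SE to actual spread of 1.29-1.31 at r = 0.5 and 1.65-1.73 at r = 0.7, with type I error of 0-1.3%.

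**4. How the excess shrinks.**
- Lower correlation, full linkage: 1.26 at r = 0.4, 1.17 at r = 0.3, 1.09 at r = 0.2.
- Half the workers in both waves: √(1.9 / (1.9 − (r − 0.05))) = 1.14 at r = 0.5 and 1.23 at r = 0.7.
- No worker in both waves: 1.0.

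**5. Units that change differently.** Assume a unit-by-time variance of 0.025 per wave (not a figure from the article), 12 units of 30 (360 workers), full linkage and r = 0.5.
- True SE: √(2 × 0.475 / 360 + 2 × 0.025 / 12) = 0.082.
- Printed model: mean SE 0.073 in simulation, hence too narrow, with type I error of about 8-9%. With no one paired it was 12%.
- Worker intercept alone: √(2 × 0.5 / 360) = 0.053, with type I error 2 × [1 − Φ(1.96 × 0.053 / 0.082)], about 21%.

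With 28 units of 9, r = 0.5 and a smaller unit-by-time variance of 0.02, the printed SE was still too wide (ratio 1.19). The direction therefore depends on unit size and on how much change varies.

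**6. Effect on the stated target.** If all 250-500 are analysed at both times, the unit-only SE gives 3.605 × 0.0872 = 0.31 at n = 250 and 3.605 × √(1.9 / 500) = 0.22 at n = 500. Both lie inside the stated 0.36 and 0.25.

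**The case against.** The strongest reply is that linkage is not established. Research Ethics calls the answers anonymous, and staff are recruited through leaders and QR codes. Without a linking code no worker term can be fitted, and with different people in the two waves there is no inflation. This stands, and it makes the size conditional.

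Second, r = 0.5-0.7 is given for six measurements in home care in Norway and Finland, not for two waves in residential care or hospital settings elsewhere. This also stands.

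Third, a journal article condenses its source, and a fuller analysis plan may add a worker term. This stands only in part: the article does not leave the random effects open, but names the levels and assigns an intercept to the unit. Fitted as printed, the model is wrong for linked data.

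Fourth, a reader might infer that the pre-post SE simply is 38-78% too wide, or that the power claim fails. The documents support neither. The first needs full linkage, the borrowed correlation and equal change in every unit. The second fails because the unit-only model still reaches the stated effects if all 250-500 contribute at both times. The power loss at d = 0.20 lies below the planned range.

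Fifth, a worker intercept on its own can do harm. This stands (step 5): leaders may adapt the Toolbox to their setting, so unequal change across units is plausible.

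**Conclusion.** The concern holds in conditional form. The printed random structure omits the correlation within a worker, so for linked surveys the SE of the time effect is miscalibrated. The upper bound is an SE 38-78% too wide. It rests on complete linkage, r = 0.5-0.7 carried over from the cluster trial, and the same change in every unit. At r = 0.3 the excess is about 17%, and with half the workers linked it is about 14-23%. If answers cannot be linked, there is nothing for a worker term to recover. If units change differently, the printed SE can be too narrow and the test too liberal. The power figures also assume 250 linked workers, whereas the 250-500 per country includes leaders and informal caregivers. The correction should be made, but the stated detectable range is not overturned by this defect alone.

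**What to change.** In Pre-Post Evaluation (Test Cases 2-4), state whether each worker's baseline and post surveys are linked, and reconcile the two statements in Research Ethics on anonymity and pseudonymization accordingly.

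- **If linked:** add a random intercept for worker nested in unit, together with a unit-by-time random effect (or unit-level cluster-robust SEs with a small-sample correction). Keep workers who answered only one survey.
- **If not linked:** call the design repeated cross-sections and include a unit-by-time term.

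In either case, state the cluster size and any within-person correlation behind d = 0.25-0.36.

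The cost is a few lines of text and a slightly more complex model. The main limit is practical: the input-phase survey serves as the pretest and its data have already been collected, so the worker term is possible only if a linking code was kept at baseline.
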